## Abstract

**Background:**

The role of physical activity in the promotion of children’s well-being and health is widely known. However, research indicates that the time spent physically exercising and participating in organized sport activities is decreasing among children. Although there is currently no gold standard for promoting sustainable physical activity in children, community-based approaches, particularly those that are multicomponent, appear to be the most successful. The project StuPs: a school- and community-based participatory approach for promoting physical activity in children and their families aims to develop a community-based approach to promoting physical activity by increasing physical literacy among elementary school children and their household members.

**Methods:**

The project is built upon the intervention mapping approach and consists of two periods with an overall duration of 3 years. Period I will last 9 months and include an assessment of needs, wants, strengths, and weaknesses regarding physical activity and health promotion at the community- and school-based level according to the keywords “capacity building” and “physical literacy.” Based on the knowledge gained in this stage, measures for capacity building to promote healthy lifestyles and physical literacy in children will be developed using the community-based participatory research and capacity building approach. In Period II, the measures will be applicated, implemented and evaluated using a pre−/post-design to assess efficacy.

**Discussion:**

Although the efficacy of using community-based and capacity building approaches to reach children is promising, there remains a gap regarding best practices for changing existing structures and habits over the long term and in the sense of promoting physical literacy.

## Background

Increasingly sedentary behavior in children constitutes a growing global challenge, although awareness of the role of physical activity in optimizing children’s health is ubiquitous [1, 2]. Despite the various health benefits of physical activity on physical, psychosocial, cognitive, motor skill, and language development [3], only 20% of children and adolescents worldwide meet the World Health Organization (WHO)‘s physical activity recommendations of 60 min per day [2]. Similar data resulted from a German health survey from 2014 to 2017 conducted by the Robert Koch Institute: only 22.4% of girls and 29.4% of boys met the WHO’s recommendations [4] - a far cry from the German physical activity recommendations of 90 min or more per day among elementary school children [5]. These data have also shown that time spent physically exercising correlates positively with socioeconomic status and negatively with age. Therefore, the challenge remains to develop efficient and sustainable strategies for promoting physical activity among children. The StuPs project: a school- and community-based participatory approach for promoting physical activity in children and their families, was developed for this purpose, particularly in response to “Bewegung und Bewegungsförderung” (“exercise and physical activity promotion”), the German Federal Ministry of Health’s call for funding [6]. The aim of this call was to spread the knowledge of the German recommendations for physical activity in the sense of health in all policies. Currently, there is no gold standard for promoting physical activity in young children, especially among vulnerable groups; despite this, school-based and multicomponent approaches are suspected to be most efficient. Because schools are the optimal environment for reaching a great number of youth demographics, school-based approaches seem to have high efficacy [5]. However, physical activity promotion in schools seems to have a limited impact on children’s movement behavior during their leisure time [7]. Current evidence assumes greater success in preventing childhood obesity if entire communities are involved in creating and promoting healthy environments [8]. The inclusion of additional out-of-school aspects within the scope of multicomponent approaches and the inclusion of families, communities, policies, and stakeholders in a participatory manner is recommended [5, 7]. Participatory approaches, such as community-based participatory research (CBPR) [9], have the potential to generate synergy, reach greater acceptance within the target group, and engender increased engagement [8, 10], especially in combination with capacity building [8, 11]. On a behavioral level, the available evidence supports an approach that promotes physical literacy, a construct that indicates the basis for an active lifestyle and serves as “a primary determinant of health and disease” [12]. Physical literacy thus focuses on skill acquisition. In this way, it is similar to the construct of health literacy, which inculcates the ability to find, understand, evaluate, and apply health information and therefore combines knowledge with motivation and competence [13, 14]. To date, no intervention combining physical literacy with community-based strategies has been conducted. Therefore, the StuPs project aims to close this gap between science and practice by implementing a participatory and interdisciplinary multicomponent approach targeting both schools and communities in two socially deprived areas in Cologne (North Rhine-Westphalia, Germany) within the scope of capacity building for physical literacy promotion.

## Methods

### Study design

The StuPs design (Fig. 1) is intended to function as a temporary supporter of the selected districts over the project duration of three years, divided into two periods. The first period (Period I) will be conducted over the course of 9 months. Using a multicomponent, mixed-methods approach, it will identify structures like geographic information system data (GIS), existing capacities, collaborations, and networks to detect needs and wants regarding physical activity promotion in children. At the end of this period, required actions will be deduced. With the knowledge of these required actions, measures to create healthy environments in the sense of capacity building and physical literacy promotion in children will be developed. This procedure will be conducted with the participation of key stakeholders in the two Cologne districts. The intention is to create measures integrable into the routines of the stakeholders, schools, and target group and address individuals as well as their environments. Therefore, these measures will on the one hand address the behaviors of children and their families as well as their districts’ capacities to create healthy environments. On the other hand, they will enable local stakeholders within the topic of health and physical literacy promotion by qualification trainings.

**Fig. 1 Fig1:**
[figure not shown]
Study Design of the StuPs Project

The intention of the second period (Period II) is to implement the developed measures over a 27-month period. Measures will be combined with existing health-related structures in terms of health in all policies. To evaluate efficacy, the status quo will be analyzed in a manner equal to that in Period I to capture changes on structural levels. To investigate behavioral changes, pre- and post-tests of the children’s physical literacy levels will be conducted. Additionally, the German Federal Ministry of Health has employed an external evaluation group [6], to investigate promoters and inhibitors during the StuPs project in the context of the call for funding “Bewegung und Bewegungsförderung”. The aim of the external evaluation is to detect factors of success within community-based approaches. At the end of Period II, a transfer guideline will be developed through an iterative and participatory process to be provided to various districts and communities; this transfer guideline will contain step-by-step instructions, serving as a best practice model, using as few resources as possible. Additionally, it will include information on how to i) capture needs and wants in terms of capacity building and physical literacy promotion in settings, districts, or communities; ii) apply and implement measures; ii) evaluate efficacy; and iv) document procedures to facilitate learning from each other regarding practical experiences. Throughout the entirety of the project, there will be cyclical, iterative reports and dialogues at the community level.

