### Participants and recruitment

The approach will be partially randomized. Participating schools from two Cologne districts (Chorweiler and Meschenich) will be recruited for this study. The two districts have been chosen because of their social circumstances, as defined by the Cologne Office for Urban Development and Statistics [15]. The index for social circumstances of urban districts is based on information related to issues such as economic deprivation, political and cultural disadvantage, and health inequality. With the support of the district coordinators responsible for social planning, two elementary schools (one in each district) will be recruited, and local networks will be identified. The elementary schools will provide access to the target group of children, parents, teachers and other pedagogical staff. Any children and parents at the chosen elementary schools will have the opportunity to participate; therefore, the target group will be composed randomly. The identified networks will be used to get in contact with local stakeholders to establish participatory collaborations.

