## Discussion

Individual habits and behaviors as well as environments (e.g., immediate surroundings, neighborhoods, schools, local policies) have a great impact on a child’s health status [19]. Therefore, healthy environments need to be created, and StuPs has been developed to achieve this aim. This approach is grounded in CBPR [9] and intervention mapping [16], both of which have evidence-based efficacy e.g. in terms of anthropometric and behavioral changes as well as environmental and political outcomes [8, 16, 17]. Previous studies have reported increasing success in terms of intensity of community engagement and participation [8, 10]. In addition, the StuPs approach has been developed following CBPR and intervention mapping to build upon existing knowledge and experiences. Although the rough procedure is comparable with other approaches, StuPs differs in its aim to improve physical literacy in children and their families. Most other community-based approaches have addressed health promotion in general or healthy weight in children specifically [8]. Currently reported physical literacy interventions have mainly been conducted in schools, especially physical education classes [20]. StuPs is unique in its aim to promote physical literacy at the community level, thereby reaching children not only where they learn but also where they live and play. This potential arises from increased scientific attention because physical literacy is assumed to be fundamental in creating physically active lifestyles [20]. According to Carney et al. [12], physical literacy is “a gateway” to lifelong physical activity and is crucial for a positive attitude toward movement. In addition to personal and individual factors such as age, gender, motor skills and psychosocial development, one’s environment is assumed to impact one’s degree of physical literacy [21]. The development of healthy environments - including walkable neighborhoods, opportunities to move and play, and opportunities to participate in sports and physical activity - could motivate and support children and families to develop active and therefore healthy lifestyles. For this reason, the intention of the StuPs project is to spread the knowledge of the physical literacy construct beyond schools and among community stakeholders, which, in combination with capacity building, will create healthy environments and therefore support children in developing more active lifestyles. It is expected that improved physical literacy knowledge among stakeholders will lead to increased readiness to change structures and build capacities for healthy environments for districts’ children. To maintain closure of the gap between science and practice in these efforts, there will be cyclical, iterative reports at the community level within specific working groups. The members of the working groups are practical experts on different community- and district-related issues, and they will support the overall project duration through discussion of any barriers and obstacles that appear. The project will benefit from their expertise and experience as well as incorporate feedback and further impulses and ideas. This will be especially helpful when preparing the transfer guideline to ensure that it is as feasible as possible. With this approach, StuPs intends to contribute knowledge of supporters and barriers to promote sustainable physical activity in the scientific interest of the German Federal Ministry of Health.

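### Repeating the Period I stocktake the same way does not separate structures the project created from structures it only came to know about

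*Protocol article*

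**What the plan says.** Under Methods, Study design, the article describes a Period I stocktake: "it will identify structures like geographic information system data (GIS), existing capacities, collaborations, and networks". Its length is given too: "The first period (Period I) will be conducted over the course of 9 months". The text after Fig. 1 then sets a 27-month Period II for implementation and defines the structural evaluation: "the status quo will be analyzed in a manner equal to that in Period I to capture changes on structural levels". That sentence opens by stating its purpose, "To evaluate efficacy, the status quo will be analyzed", so the repeat is the efficacy reading at structural level. Children's physical literacy is tested separately, before and after.

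Three other places bear on what happens between the two readings:
- Study design says of the measures that "they will enable local stakeholders within the topic of health and physical literacy promotion by qualification trainings".
- Participants and recruitment says that "The identified networks will be used to get in contact with local stakeholders to establish participatory collaborations".
- The Discussion expects that "improved physical literacy knowledge among stakeholders will lead to increased readiness to change structures".

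Both named districts receive the measures. No comparison district is described.

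**The concern.** A before/after inventory measures change only if both readings find existing items equally well. Here the project itself may alter how well they are found. At Period I the team is still locating networks and making contacts. By the repeat it has worked in the districts for more than two years, and local stakeholders have been trained and brought together. An offer that was running before Period I but went unnoticed could then surface in the second reading and look like a result of the project.

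District capacity is one of the things the measures are meant to change. The transfer guideline is to serve as a model for other districts and to tell them how to evaluate efficacy. A structural result inflated by better detection would overstate what the approach achieves, and the same way of evaluating would be passed on.

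**Working it through.** The article gives no number of structures, so there is no figure to reproduce. The check is a reading of the text, followed by a conditional illustration.

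**What differs between the two readings**
- Method: the same at both, by design (Study design, text after Fig. 1).
- Project access: at Period I, local networks are being identified with the support of district coordinators (Participants and recruitment). By the repeat, collaborations have been set up, reports and dialogues have run throughout, and working groups of local experts have met over the project's duration (Study design; Discussion).
- Stakeholder knowledge: qualification training lies between the readings (Study design), and the Discussion expects knowledge to improve.
- Concurrent control: none described.
- Rule for dating items or matching them to the Period I list: none described. Data management and analysis specifies qualitative analysis for Period I. The external evaluation is directed at promoters and inhibitors and is not described as an independent inventory.

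So the text gives reasons why detection may improve, and describes nothing that would separate newly found from newly created.

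**Illustration (all detection rates are assumptions)**

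Let the true set of offers be unchanged. Let s1 be the proportion found at Period I and s2 the proportion found at the repeat, with finds independent. Then:
- apparent net change = s2/s1 − 1
- listed as new, per 100 true offers = 100 × (1 − s1) × s2
- listed as lost, per 100 true offers = 100 × s1 × (1 − s2)

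| s1 | s2 | Listed as new | Listed as lost | Apparent net change |
|---|---|---|---|---|
| 0.60 | 0.90 | 36 | 6 | +50.0% |
| 0.70 | 0.90 | 27 | 7 | +28.6% |
| 0.80 | 0.90 | 18 | 8 | +12.5% |
| 0.90 | 0.95 | 9.5 | 4.5 | +5.6% |
| 0.80 | 0.80 | 16 | 16 | 0% |

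For the third row: 100 × 0.20 × 0.90 = 18 new, 100 × 0.80 × 0.10 = 8 lost, and (18 − 8)/80 = 12.5%.

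Two things follow. A net upward error arises only if detection improves. And even with equal detection, an undated comparison lists items as new and as lost when nothing has changed.

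**The case against.** The strongest reply is that the informants of the stocktake are not named. A reader might infer that the inventory draws on the same stakeholders who are later trained. The sentence that suggests this, "This procedure will be conducted with the participation of key stakeholders in the two Cologne districts", follows the one on developing measures and most directly refers to that step. In Table 1, Step 1 (the inventory) mentions no stakeholders; they first appear in Step 2. Period I also uses several methods and includes GIS data, which do not depend on anyone's recall. This stands: reliance on trained informants is an inference. It is a reasonable one for collaborations and networks, which are hard to establish without local knowledge, and weak for GIS items. The point does not depend on it entirely, because the team's own access also changes.

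Second, no count is planned. The article describes qualitative analysis, and a qualitative comparison need not subtract one list from another. This also stands, and it is why the table above says nothing about the likely size here. A qualitative reading is still open to the same error if an old offer is described as a new one.

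Third, the direction is not certain: trained stakeholders might apply stricter standards and report less capacity. That is possible. The text points more towards better detection, but does not prove it.

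Fourth, stakeholders who become skilled and connected are part of what the project sets out to achieve. This is correct, and such change should be credited. The point is confined to items that already existed and were missed.

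Fifth, dialogues and working groups give the team ways to learn of missed offers. They do, but they improve later detection without correcting the Period I list.

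Finally, dating rules may sit in the full protocol, which is not shown. That is so. The point rests on the comparison the article does fix, an equal-method repeat without a described comparison district, and not on a missing form field.

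**Conclusion.** The point holds in a limited form. The structural efficacy reading is a repeat of the Period I analysis by the same method, after an intervention that can change how completely existing structures are known. Offers that pre-date Period I can therefore be read as structural change, and the article describes nothing that would tell the two apart.

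A reader might go further and conclude that missed offers will be counted as new capacity, or that the error must favour the project. The article does not support either. It plans no count, does not name the informants, and an upward error requires detection to improve between the readings. The size is not derivable; under the assumed detection rates the apparent gain ranges from 0% to 50%. GIS-based items are less exposed, and links or skills that the project creates are real change.

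**What to change.** At the Period II stocktake:
1. For each structure, collaboration or offer, record when it began, with a documentary source where one exists (for example a district record, GIS layer, school programme or cooperation agreement).
2. Add items that pre-date Period I back to the Period I inventory before comparing.
3. Report newly created items and newly found items separately.
4. Report stakeholders' perceived capacity and readiness separately, as perception.

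This remains possible after Period I has closed and needs no new arm or sample. The cost is slightly more documentation and a revision of the Period I list. Start dates will sometimes be recalled imperfectly, so undated items should be shown as such. The structural result may be less favourable. If detection did not in fact improve, the net result should change little.

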### Data management and analysis

Any conducted assessments will be carried out anonymously. The results of Period I will be analyzed and interpreted by conducting qualitative data analysis [18] in the MAXQDA 2020 software. The data resulting from the children and parental pre- and post-tests will be analyzed using the SPSS software version 27.0 (SPSS Inc., Chicago, IL, USA). The significance level α will be set at < .05; confidence intervals will be estimated at 95%. Descriptive analysis will be conducted to identify cross-sectional and long-term changes in physical literacy level, including motor skills, by generating means and variances. Additionally, correlations and influencing factors among variables will be assessed using analysis of covariance and regressions.

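### An uncontrolled pre/post comparison, with no measurement after support ends, is presented as an assessment of efficacy

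*Protocol article*

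**What the plan says.** The Abstract (Methods) says that in Period II "the measures will be applicated, implemented and evaluated using a pre−/post-design to assess efficacy". The Study design section repeats the aim for the structural level: "To evaluate efficacy, the status quo will be analyzed in a manner equal to that in Period I to capture changes on structural levels". For the children it names a pre-test and a post-test of physical literacy and no later measurement.

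On the units, Participants and recruitment says "two elementary schools (one in each district) will be recruited, and local networks will be identified", and the Background describes an approach "targeting both schools and communities in two socially deprived areas in Cologne". The recruitment section calls the approach partially randomized. Its explanation is that any children and parents at those schools "will have the opportunity to participate; therefore, the target group will be composed randomly".

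On time, the design is "intended to function as a temporary supporter of the selected districts over the project duration of three years", divided into Period I of 9 months and Period II of 27 months. Under Data management and analysis, a descriptive analysis is to "identify cross-sectional and long-term changes in physical literacy level". A transfer guideline for other districts and communities is to follow at the end of Period II: "this transfer guideline will contain step-by-step instructions, serving as a best practice model, using as few resources as possible".

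**The concern.** Efficacy is a causal claim: the children or the districts changed because of the measures. To support it, a design must say what would have happened without them. Here both districts receive the measures and nothing stands in for the untreated course.

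The article itself supplies rival explanations. The Discussion lists age, motor skills and psychosocial development among the factors for physical literacy. The Background reports that exercise time falls with age. The Study design section says the measures will be combined with health-related structures that already exist. Repeating the same tests adds a further possible source of change.

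The project also describes itself as temporary support, and the Abstract's Discussion names change over the long term as the open question. Whether anything lasts after support is withdrawn is not observed. At stake is how the result is reported and what other communities are told when they receive the guideline.

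**Working it through.** **1. Is there a comparator?** The relevant statements side by side:
- Schools: two, one per district (Participants and recruitment).
- Districts: both are targeted by the measures (Background).
- Randomization: the word is attached to open, voluntary participation within the chosen schools. Nobody is allocated to an arm.
- Control school, control district or external reference series: none is described.

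The pre/post difference therefore equals the effect of the measures plus ageing, secular change, other programmes and re-testing. The described data give no means of splitting that sum. The structural re-assessment has the same form: the same two districts, before and after.

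**2. Does the timeline leave room after support ends?** Inputs from Study design: project and support 3 years, Period I 9 months, Period II 27 months.
- 3 × 12 = 36 months; 9 + 27 = 36 months. The article's figure is reproduced.
- 36 − 9 − 27 = 0 months after Period II.

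Any post-test or structural re-assessment within the project thus falls while support is running. The pre-to-post interval is at most about 27 months if the pre-test opens Period II, and at most 36 months if it falls in Period I. The test dates are not stated.

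**3. How easily could drift look like an effect?** This is an illustration only, because the article gives no sample size, effect size or pre/post correlation. Assumptions: a paired comparison of n linked, independent children, correlation r between pre- and post-test, two-sided α = 0.05 (the article gives .05 without sidedness), a true intervention effect of zero, and a background drift of d standard deviations. With the normal approximation,

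P(significant) = Φ(d·√(n/(2(1−r))) − 1.96) + Φ(−d·√(n/(2(1−r))) − 1.96).

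Example: n = 100, r = 0.5, d = 0.3. Then √(100/1) = 10, 0.3 × 10 = 3, and Φ(1.04) + Φ(−4.96) = 0.85.

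| n | r | d = 0 | 0.1 | 0.2 | 0.3 | 0.5 |
|---|---|---|---|---|---|---|
| 50 | 0.5 | 0.05 | 0.11 | 0.29 | 0.56 | 0.94 |
| 50 | 0.7 | 0.05 | 0.15 | 0.45 | 0.78 | 1.00 |
| 100 | 0.5 | 0.05 | 0.17 | 0.52 | 0.85 | 1.00 |
| 100 | 0.7 | 0.05 | 0.25 | 0.73 | 0.97 | 1.00 |
| 200 | 0.5 | 0.05 | 0.29 | 0.81 | 0.99 | 1.00 |
| 200 | 0.7 | 0.05 | 0.45 | 0.96 | 1.00 | 1.00 |

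The nominal 0.05 holds only at zero drift. More children make the problem worse, because they estimate the mixed quantity more precisely.

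**The case against.** The best defence is that this is a participatory two-district project reported in a condensed article, and that several stronger criticisms are not in the text. Most of that stands.

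- *The guideline will be issued as best practice whatever the evaluation shows.* A reader might infer this because no success criterion is stated. The article does not say so. Step 6 of Table 1 puts review and evaluation together with transfer indicators, an external group studies promoters and inhibitors, and working-group feedback informs the guideline. Silence is not a commitment to ignore a null result. The guideline's listed contents are also largely procedural. What remains is that the label best practice model, set beside an efficacy evaluation, suggests a demonstration that the design cannot give.
- *The article claims lasting effects.* The analysis section pairs long-term with cross-sectional, so the phrase can simply mean change over time. The design can describe raw change over up to about 27 to 36 months. The phrase is ambiguous rather than false.
- *Exposure at post-test is well short of 27 months.* This is plausible, since re-assessment and guideline work also have to fit in Period II. But the article never states an exposure time, and any figure would rest on an assumed duration for that work.
- *A comparator may exist in the full protocol or in Fig. 1, which is not shown.* Possible, but a control arm is not a detail that an article normally leaves out, and the text points the other way.

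None of this answers the central point. The word efficacy is used for both the behavioral and the structural evaluation, and the described design cannot support it.

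**Conclusion.** The concern holds as a mismatch between claim and design. The study can describe change in the two schools and districts while support is running. It cannot attribute that change to the measures, and with 0 of 36 months left after Period II it cannot show persistence.

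The timeline result is exact. The absence of a comparator is read from the text. The size of any bias is unknown: the probabilities at 0.3 SD drift (0.56 to 1.00) depend on assumed n, r and drift, and show only that a significant pre/post change would be weak evidence of an effect. The documents do not support going further and saying that the plan would promote a failed programme or that it claims post-support effects. The correction is worth making because it changes what the study may conclude and needs no new data.

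**What to change.** Change the wording in three places of the article:
1. Abstract (Methods) and Study design: replace the statements that efficacy is assessed or evaluated with *describe uncontrolled change during the supported phase*, for the children and for the structures.
2. Data management and analysis: replace long-term changes with *changes between pre- and post-test*.
3. Study design, guideline paragraph: describe the guideline as *reporting implementation experience together with the observed uncontrolled change*, not as a best practice model resting on shown efficacy.

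Do not try to keep the label through a rule that grants it when the 95% interval for the pre/post change excludes no change. Drift or another local programme could satisfy that rule with no effect of the measures, as the table shows for drift.

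The cost is protocol wording only. Recruitment, measurements and analyses stay as they are. The downside is that the stated claim becomes less favourable.
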